#### Control group

The control group will receive physical activity counseling, provided by reinforcing the information of the video they watched prior to randomization.

#### Group 3 – App + tailored messages + gamification II

The second stage of gamification will be available in the protocol by the time of the intermediate assessment (6th week of intervention). Gamification II will include the same features of gamification I, plus opportunities for socialization among participants (biweekly group meetings) and discussion forums about physical activity.

### Defining responders and non-responders

The American College of Sports Medicine recommendations about the quantity and intensity of physical activity suggest increases of 2000 steps per day to achieve improvements in cardiovascular health [15]. After a pre-test with persons from researchers’ networks using a smartphone app with a pedometer, we observed that the target of increasing 2000 steps/day would not be realistic to our population. Therefore, we decided to plot the average number of steps of participants in a graph using a linear tendency line and participants that present a positive slope, i.e., a tendency to increase step counts, will be considered as responders. Consequently, participants with a zero or negative slope, i.e., a tendency to maintain or decrease step counts, will be considered as non-responders. Additionally, we will use the app’s first-week step count as a reference for both sending the tailored messages and analyzing participants’ slopes. Thus, we believe that this way we will be able to set individualized and feasible goals for our population.

#### Intermediate assessment

The intermediate assessment to identify responders and non-responders will take place at week 6 from the beginning of the protocol. We will calculate the average number of steps/day from weeks 1 to 6, and compare with the number of steps/day from the initial assessment. Participants identified as non-responders will then be re-randomized and will receive instructions about the new phase of intervention (Fig. 1). We will collect the average number of steps per day using the app interface; all participants will use the app for 1 week after randomization prior to any intervention and we will consider the step count from the first week as a comparator for weekly and intermediate assessments.

### Follow-up

After 3 months of intervention, all participants (including those in the control group) will be reassessed. Participants from groups 1, 2, and 3 will be advised to maintain the monitoring of daily steps by the app but will no longer receive any direct intervention from researchers (text messages, virtual challenges, or group meetings). Finally, after 3 months of self-monitoring of the number of steps, all participants will be reassessed and the protocol completed.

### Sample size

The main objective of a SMART study relies on the feasibility of carrying out a future large-scale trial, rather than investigating the effects of the proposed set of treatments. To reach this goal, we must ensure that the number of subjects will be sufficient and balanced among all of the subgroups. According to Almirall et al. [16], a fixed probability *k* of about 80–90% should be considered so that at least *m* participants would end in non-responders’ subgroups B, C, E and F (Fig. 1). Considering a range of non-response rates in SMART studies of 35–65%, we calculated an *m* of 3 participants per subgroup as sufficient to ensure familiarity with the protocol, treatment delivery, and identification of potential problems. For a non-response rate of q = 50% at the end of the 6th week, our pilot SMART study will require 42 participants (14 per arm) [16].

After conducting this SMART pilot, we will consider the variation on the average number of steps per day to calculate the sample size of the trial, including an up to 40% loss to follow-up and a less optimistic non-response rate of 65%. To increase the feasibility of a future large-scale trial, we will calculate the sample size considering groups A + B (maintain – switch to group 2), groups A + C (maintain – switch to group 3), groups D + E (maintain – switch to group 1), groups D + F (maintain – switch to group 3), and the control group.

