## Discussion

To our knowledge, this will be the first trial with an adaptive intervention to test the effectiveness of using a smartphone app to increase the level of physical activity of adults and older adults. As stated above, the SMART design has been recommended over the classical randomized controlled trial for technology-based interventions [12, 13].

One of the major challenges of the present study will be to engage Brazilians to track their daily steps using technology. Despite the large number of smartphones in use in Brazil, whether the proposed application will be effective in this population needs more clarification. Another challenge will be the lack of security to carry out outdoors physical activities in Brazil, regardless of the neighborhood. In our recent experience, many participants from our pre-test reported not using a smartphone when practicing physical activity outdoors. We believe that creating favorable conditions for behavior change and the adoption of a healthy lifestyle will favor adherence and engagement of those involved in the study. Using the technology available on a smartphone to encourage the adoption of new ways of thinking and acting can be a new way of promoting the quality of life and well-being of the Brazilian population.

Finally, the sample size required for SMART studies is usually large and difficult to calculate. We are aware of the difficulty of involving enough people in a tight timeline. However, we are confident that we are prepared to run the protocol with sufficient statistical power, at least for some key health variables.

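### Fourteen per arm gives a 79% chance of filling both non-responder subgroups in one arm, but 62% for all four, and the plan does not say which event its 80–90% covers

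*Protocol article*

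**What the plan says.** The Sample size section of the protocol article says that the pilot serves feasibility rather than the estimation of effects, and that numbers must be adequate and balanced across the subgroups. Its criterion is a fixed probability k "of about 80–90% should be considered so that at least" m participants end in the non-responder "subgroups B, C, E and F". Subgroups B and C come from Group 1, and E and F from Group 2.

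The inputs are:
- an m "of 3 participants per subgroup as sufficient to ensure familiarity with the protocol, treatment delivery, and identification of potential problems";
- a span of plausible rates, "Considering a range of non-response rates in SMART studies of 35–65"%;
- a planning value, "For a non-response rate of q = 50% at the end of the 6th week".

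The result is "our pilot SMART study will require 42 participants (14 per arm"). The section does not give the k that 14 per arm achieves, and does not say whether k applies to one arm or to all four subgroups together.

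The later trial is to be sized after the pilot, "including an up to 40% loss to follow-up and a less optimistic non-response rate of 65"%. The Discussion closes with "we are confident that we are prepared to run the protocol with sufficient statistical power, at least for some key health variables".

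**The concern.** Filling the non-responder subgroups is the only sizing criterion the pilot has. The sentence that sets it names four subgroups across two arms, so the natural reading is that all four must reach 3. A size that meets the target within one arm need not meet it in both at once.

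If the joint reading is intended, the pilot misses its own target at its own planning value, and a reader would overestimate how likely it is that every re-randomised path is tried on at least 3 people. What is at stake is the feasibility information from the thinnest subgroups. No treatment estimate is biased by this.

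A smaller point is that the Discussion speaks of sufficient power, while the only sample size in the article was not derived from power.

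**Working it through.** **Inputs from the Sample size section.** n = 14 per arm, two app arms, m = 3, q = 50% (range 35–65%), target k about 80–90%.

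**Assumptions the article does not state.** Non-responders in each arm are re-randomised 1:1 and split as evenly as possible. Nobody is lost before week 6. The two arms are independent and share the same q.

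**Formula.** The number of non-responders in an arm is M ~ Bin(n, q). Under an even split, both subgroups of that arm reach m exactly when M ≥ 2m = 6. So

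P(arm) = 1 − Σ C(n, i) q^i (1 − q)^(n − i), summed over i = 0 to 5, and P(all four) = P(arm)².

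**Reproducing 14 per arm at q = 50%.**
- Σ C(14, i) for i = 0 to 5 is 1 + 14 + 91 + 364 + 1001 + 2002 = 3473, and 2^14 = 16384.
- P(arm) = 1 − 3473/16384 = 0.788.
- P(all four) = 0.788² = 0.621.

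The per-arm figure is within 2 points of 80%, which probably explains the 14. The joint figure is well below the target range.

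**Other sizes at q = 50%, m = 3.**

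| n per arm | Total, three arms | One arm | All four subgroups |
|---|---|---|---|
| 14 | 42 | 78.8% | 62.1% |
| 15 | 45 | 84.9% | 72.1% |
| 16 | 48 | 89.5% | 80.1% |
| 17 | 51 | 92.8% | 86.2% |
| 18 | 54 | 95.2% | 90.6% |

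**The stated range of q, with 14 per arm and m = 3.**

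| q | One arm | All four subgroups |
|---|---|---|
| 35% | 36.0% | 12.9% |
| 50% | 78.8% | 62.1% |
| 65% | 97.6% | 95.2% |

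For filling non-responder subgroups, low non-response is the unfavourable direction.

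**A lower m.** With m = 2 an arm needs at least 4 non-responders. P(arm) = 1 − (1 + 14 + 91 + 364)/16384 = 1 − 470/16384 = 0.971, and squared this is 0.943.

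**Pooling the arms.** At least 12 non-responders among 28 has probability 82.8% at q = 50%. That does not ensure 3 in each subgroup, because 12 can fall unevenly between the arms.

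**How far the best case matters (illustrations on assumed inputs only).** If each non-responder were allocated by an independent 1:1 draw with no balancing, the joint probability would be 23.4%. If 20% were lost before week 6, the effective rate would be 0.5 × 0.8 = 0.40, with P(arm) = 0.514 and a joint probability of 0.264. The article states neither input. These figures show only that departures from the assumptions lower the 62.1%.

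**The power remark.** No arithmetic applies. The Sample size section disclaims effect testing for the pilot and postpones the trial's calculation. The Discussion expresses confidence in power for some variables. No effect size, variance, alpha or target power is given to connect the two.

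**The case against.** The best defence is that the section only recommends considering a k of about 80–90%. It does not claim that 14 per arm delivers that jointly, and the source of the method is not visible here. Read per arm, 78.8% is a fair match to about 80%. This stands as the likely origin of the 14, and it is why one cannot simply say that the number was miscalculated. It does not settle the matter, because the sentence lists all four subgroups and the section asks for adequate numbers in every one, without saying that k is per arm.

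The consequence is also modest. On the same assumptions every non-responder subgroup holds at least 2 people with 94% probability, and this is a feasibility pilot.

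A reader might draw several stronger conclusions that the article does not support:
- *That 42 participants are presented as adequately powered.* The Discussion does not tie its remark to 42, and limits it to some variables. On the literature effect of 0.54 in Background and an assumed two-sided 5% level, 14 against 14 has 28% power, but neither figure is a design input. A standardised effect of about 1.10 would have 80% power, so the remark is unsupported rather than shown to be false.
- *That 40% loss is expected in the pilot's first six weeks.* The 40% is an upper allowance for sizing the later trial.
- *That q = 50% is an error.* It is a declared planning value inside the stated range.
- *That the second randomisation is unbalanced.* The article gives blocks for the first allocation and no detail for the second. A condensed article may leave that to the full protocol.

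**Conclusion.** The point holds as a matter of definition and reporting. At the plan's own inputs, 14 per arm gives 78.8% for one arm and 62.1% for all four subgroups, a shortfall of about 18 points from the lower end of 80–90% on the joint reading. The joint chance of missing the target is about 38% at q = 50%. It rises to 87% at q = 35% and falls to 5% at q = 65%.

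The arithmetic is exact given an even second-stage split, no loss before week 6, and independent arms with a common q. What remains uncertain is which event the authors meant by k. The text favours the joint event, while the number fits the per-arm event. The section should be corrected, but the defect does not threaten the validity of the pilot.

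The Discussion's power remark is a secondary inconsistency: it has no stated basis and sits badly with a sample size set for feasibility.

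**What to change.** Keep 42 participants. In Sample size, state which event k covers and replace the implied 80–90% with what the design delivers, for example:

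> With 14 per arm and m = 3, k is 79% within each app arm and 62% for all four non-responder subgroups jointly at q = 50% (jointly 13% at q = 35% and 95% at q = 65%). With m = 2 the joint k is 94% at q = 50%. These figures assume an even second-stage split within each arm and no loss before week 6.

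In the Discussion, delete the remark on sufficient power or limit it to the later trial, whose size is still to be calculated.

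The cost is a few restated figures and a stated k that looks less favourable. No participants are added. If the sponsor instead wants the joint criterion met at q = 50%, that takes 16 per arm (48 in total, 6 more) for 80%, or 18 per arm (54 in total, 12 more) for 90%, on the same assumptions.

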### Aims and design

The primary aim of our study is to investigate the effect of a smartphone app combined with game elements on the level of physical activity of adults and older adults, measured by the average number of daily steps. The secondary aims are (1) to verify the effects of the intervention on cardiometabolic and cardiovascular health, lung function, and cardiorespiratory fitness; and (2) to verify the relationship between age group and the response rate.

We will conduct a Sequential Multiple Assignment Randomized Trial (SMART). This study was approved by the Ethics Committee of the Federal University of Sao Paulo (# 0499/2018) and is registered in the Brazilian Clinical Trials Registry (RBR-8xtc9c).

The SMART design has been recommended over the classical randomized controlled trial for technology-based interventions [12, 13] as it allows adaptations over time based on the participants’ response to the intervention. Despite the large potential and shown feasibility [14], the SMART design has, thus far, hardly been conducted in smartphone and gamified interventions.

The adaptive intervention protocol will last 6 months. Initially, participants will be randomized into one of three groups (group 1: app + tailored messages; group 2: app + tailored messages + gamification I; control group: physical activity counseling) (Fig. 1). Over 12 weeks, we will record the average number of steps per day for each participant from groups 1 and 2. At 6 weeks from initiation, participants will be classified into responders and non-responders according to the targeted average number of daily steps; all those considered as non-responders will be re-randomized, with the chance to participate in a third group – group 3: app + tailored messages + gamification II (Fig. 1). At the end of the 12 weeks, participants will continue using the app but will no longer receive any direct intervention from investigators. All participants, including those in the control group, will be reassessed at 3 and 6 months from baseline. The protocol timeline is shown in Fig. 2.

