**Fig. 2 Fig2:**
[figure not shown]
SPIRIT figure – protocol timeline

Assessors will be blinded to group allocation. We will randomize participants in blocks of six (two to each group) using opaque sealed envelopes and the sequence of group allocation will be computer generated.

Before randomization, all participants will watch a brief animated video about the benefits of practicing physical activity, the minimum quantity of exercise recommended to reach health benefits, and examples of daily-living situations where they can increase their levels of physical activity. They will receive a link to watch the video on the internet as many times as they want and will receive a printed booklet with the same content of the video.

Participants from groups 1 and 2 will have a commercial freely available app installed on their smartphones. This app has gamification functionalities, and it will track their daily steps. Participants will be instructed about the use and functionalities of the app, and they will be encouraged to use the smartphone close to their waist during all activities.

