### Interventions

#### Group 1 – App + tailored messages

Participants will use the app to track the number of daily steps and they will receive weekly text messages on their smartphones, with information about their performance on last week and motivational phrases according to their behavior-change status at the end of the protocol, the responders of Group 1 will end up in the subgroup A, while non-responders will end up in the subgroups B or C.

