#### Group 2 – App + tailored messages + gamification I

Additionally to monitoring the number of steps and individual messages, participants will be encouraged to join virtual challenges; for each challenge they complete, a virtual badge will be given. The challenges available will be related to the target number of steps per day, target distance walked in the month, and group competitions where the total number of steps is compared among the different groups of app users. Further, there will be rankings of the number of steps among all users at the end of the protocol, the responders of Group 2 will end up in the subgroup D, while non-responders will end up in the subgroups E or F.

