### Data analysis

Participants’ characteristics will be presented by descriptive statistics. We will use ANOVA tests to compare the effect of interventions on the increase of physical activity levels, cardiovascular and metabolic health, lung function, and cardiorespiratory fitness among groups A + B + C and D + E + F pre- and post-intervention compared to the control group. Additionally, we will use the same test to analyze the effect of interventions on the average number of daily steps comparing the final subgroups (A to F) against the control group as well as the subgroups A + F, B + D and C + E against the control group.

To analyze the relationship between age and the response rate to each intervention, we will group responders and non-responders according to age ranges (20–30 years old, 31–40, 41–50, 51–60, 61–70, and 71 and older) and compare them in subgroups from A to F using Pearson or Spearman correlations (according to data distribution).

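### The trial is to be sized on four adaptive strategies that the analysis section never compares, and the ANOVA named there, without weights, would not estimate them

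*Protocol article*

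**What the plan says.** Only part of each first-stage arm is randomised a second time. At week 6, "all those considered as non-responders will be re-randomized, with the chance to participate in a third group" (Aims and design). The intervention sections name the resulting subgroups: "the responders of Group 1 will end up in the subgroup A, while non-responders will end up in the subgroups B or C", and "the responders of Group 2 will end up in the subgroup D, while non-responders will end up in the subgroups E or F".

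For the trial that follows the pilot, the Sample size section states "we will calculate the sample size considering groups A + B (maintain – switch to group 2), groups A + C (maintain – switch to group 3" and continues with "groups D + E (maintain – switch to group 1), groups D + F (maintain – switch to group 3), and the control group". A 65% non-response rate and up to 40% loss to follow-up enter that calculation. No formula, power, effect size or weighting is given.

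The Data analysis section compares A + B + C and D + E + F with control by ANOVA. It then adds: "Additionally, we will use the same test to analyze the effect of interventions on the average number of daily steps", for each of A to F against control and for A + F, B + D and C + E against control. Apart from correlations with age, no other method and no weights are mentioned.

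**The concern.** The sizing and the analysis address different questions. The sizing pools are complete strategies: stay on the first option if responding, otherwise switch to a named second option. The analysis pools are not.

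The design also makes plain pooling unsafe. All responders of group 1 are in A, and A belongs to two strategies; the non-responders are divided between B and C. The same holds for D, E and F. A plain count or mean of A + B therefore has too many responders for the strategy that it stands for. Responders are defined by a rising step count, the primary outcome is average daily steps, and control is never divided by response. If responders keep higher step counts, a plain strategy pool would look better than control even with no treatment effect.

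**Working it through.** **1. Which comparisons appear where.**

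| Comparison | Sample size | Data analysis |
|---|---|---|
| Strategies A + B, A + C, D + E, D + F | yes | no |
| Whole arms A + B + C, D + E + F | no | yes |
| A to F singly | no | yes |
| A + F, B + D, C + E | no | yes |

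By the labels in the Sample size section:
- A + F joins group 1 responders to group 2 non-responders switched to group 3.
- B + D joins group 1 non-responders switched to group 2 to group 2 responders.
- C + E holds non-responders only, switched to groups 3 and 1.

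None is a strategy. Each of A to F alone is selected by response, while control is not.

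**2. Inputs.** Non-response q = 65% for the later trial, with 35% and 50% also used in the Sample size section. First-stage allocation is equal: "We will randomize participants in blocks of six (two to each group" in each block. The text does not state the second-stage ratio and Fig. 1 is not shown. I assume 1:1, in line with the aim that "we must ensure that the number of subjects will be sufficient and balanced among all of the subgroups". The only stated size, 42 (3 × 14), is for the pilot, so there is no figure for the later trial to reproduce.

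**3. Composition of a plain pool.** Share of the arm = (1 − q) + q/2. Responder share of the pool = (1 − q)/(1 − q/2). The shift in the pool mean is the excess responder share times the responder/non-responder difference.

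| q | Pool share of arm | Responders in pool | Responders under strategy | Shift × difference |
|---|---|---|---|---|
| 35% | 82.5% | 78.8% | 65% | 0.138 |
| 50% | 75.0% | 66.7% | 50% | 0.167 |
| 65% | 67.5% | 51.9% | 35% | 0.169 |

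At q = 65%: 0.35/0.675 = 0.519, and 0.519 − 0.35 = 0.169.

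**4. What a plain test of a strategy pool would do (illustration).** Assume no treatment effect, overall SD 1, arm of 95, pool of about 64, control of 64, and a responder/non-responder difference d. The standard error is √(2/64) = 0.177.
- d = 0.5: the shift is 0.084, or 0.48 standard errors, and a 5% two-sided test rejects in about 7.6% of trials.
- d = 1: the shift is 0.169, or 0.95 standard errors, and it rejects in about 15%.

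Two simulations of 20,000 trials gave 7.6% and 7.5% at d = 0.5, and 14.7% and 15.2% at d = 1. With weights the rates were 5.4% and 5.0%, then 4.7% and 4.8%. The values of d are assumptions.

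**5. Sizing.** With weights 1 for responders and 2 for non-responders, the variance factor per arm is (1 − q) + 2q = 1 + q = 1.65 when d = 0. By head count it is 1/0.675 = 1.48. The ratio is 1.65 × 0.675 = 1.11.
- Two strategies from different first-stage arms, sized for 80% by head count: 2.80 × √(1.48/1.65) = 2.65, which is about 76% power.
- Strategy against control: 2.80 × √(2/(1 + 1.11)) = 2.73, about 78%, if control equals the pool in size; 2.80 × √(2.48/2.65) = 2.71, about 77%, if control equals a whole arm.
- With overall SD 1 and an evenly split re-randomisation, the factor is 1.65(1 − 0.2275d²) + 0.2275d², where 0.2275 = 0.65 × 0.35. It is 1.65, 1.61 and 1.50 at d = 0, 0.5 and 1. At d = 1 power between strategies is about 79.5% (77% with simple re-randomisation).

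At an assumed standardised effect of 0.5, with 80% power and two-sided 5%, comparing two strategies from different arms needs 94 per arm by head count and 104 weighted; dividing by 0.6 for 40% loss gives 157 and 174.

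**The case against.** A reader might infer that the four pools and control are to be sized and tested as five plain groups. The article does not say so. It labels each pool as a strategy and brings the non-response rate into the calculation, which is the input a strategy-level sizing needs. Choosing these pools is right for the design. This part of the objection stands.

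It also stands that ANOVA is never applied to A + B, A + C, D + E or D + F. The rejection rates in step 4 describe a test that the document does not plan. They show why weights are needed, not an error rate of the trial. Nor do the two harms peak together: the 76% power belongs to d = 0, where there is no bias, and the 15% rejection to d = 1, where almost no power is lost. How far a slope over about six weeks predicts steps at 3 or 6 months is unknown.

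It can further be said that a condensed article leaves weights and variance formulas to fuller documents. That is fair for the formulas. It does not cover the mismatch, because the Data analysis section does list its comparisons and they are not those used for sizing.

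Finally, A + F, B + D and C + E may be meant as groups sharing a final treatment. By the Sample size labels only B + D does; all three would if E and F were interchanged. Even then they would combine people selected by response from different arms, without matching a strategy.

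**Conclusion.** The point holds as an inconsistency with a methodological consequence. The strategies that determine the trial's size have no matching analysis, and the ANOVA on single subgroups and on A + F, B + D and C + E cannot give valid strategy comparisons. The whole-arm comparisons of A + B + C and D + E + F with control keep the randomised groups intact and do not have this problem.

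The direction of the composition effect does not depend on the 1:1 assumption, since any split leaves some non-responders, and no responders, out of a pool; its size does. Bias against control exists only if responders and non-responders differ at the outcome, and favours the intervention if responders keep higher step counts. The sizing loss at q = 65%, relative to head-count sizing, is modest and largest when the two do not differ. The pilot of 42 is unaffected.

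**What to change.** In Data analysis, replace the ANOVA on A + F, B + D and C + E with a comparison of the four strategies, with each other and with control, by inverse-probability-weighted regression with robust standard errors. Responders get weight 1 and contribute to both strategies of their arm. Non-responders are weighted by the inverse of the actual re-randomisation probability, which is 2 if the split is 1:1. Keep A + B + C and D + E + F against control as whole-arm comparisons.

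In Sample size, state that the later calculation uses the matching variance factor: about 1 + q per first-stage arm if 1:1, so up to 1.65 at q = 65%, in place of 1.48 by head count. Check the labels E and F against Fig. 1 at the same time.

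The cost is wording in two sections and a standard weighted model, with slightly larger standard errors and a sizing factor up to about 11% higher at q = 65%. The later trial has not yet been sized, so no stated figure has to be withdrawn.
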